##### Surveillance

FAARM’s surveillance system in intervention and control households contains three components explained in detail below: (1) routine assessment, (2) food consumption assessment and (3) birth registration (figure 3). It serves to examine indicators on the two main pathways, diet and infection, through which the intervention could impact child undernutrition, as well as assessing maternal undernutrition and intrauterine growth retardation (figure 4). All surveillance activities are conducted by locally recruited, female data collectors. Extensive training with field practice is provided before any data collector begins work. Before each 2-month data collection period, a refresher training of 1–2 days is held to review and troubleshoot as well as train on any questionnaire aspects that have been added or changed. Participants are identified for interviews using project ID cards or by verifying the names of the participant, husband and household head. Collected data are reviewed regularly for real-time monitoring and analysis. The surveillance system is summarised in table 1, while information on indicators collected is available in online supplementary table 1.

10.1136/bmjopen-2019-031037.supp2Supplementary data

A routine assessment round is completed every 2 months. Women report their last menstrual periods using provided calendars to mark the day. Pregnancies are identified with the help of pregnancy tests, which are provided for free to women for voluntary self-administration. Pregnant women are asked about antenatal care, and their weight and mid-upper arm circumference are measured at every visit, while non-pregnant women are weighed once per year. Dietary diversity information is recorded from all pregnant women each round and from non-pregnant women every 6 months, using 21 food groups.^26^ The Edinburgh Perinatal/Postnatal Depression Scale is administered during pregnancy, shortly after delivery, and after the child has attained 6 months of age.^27 28^ For all children who are below 3 years of age (at the first day of each 2-month round), we ask mothers about recent diarrhoea and acute respiratory infection episodes. Mothers of children 0–18 months are asked all questions from the standard WHO Infant and Young Child Feeding survey module each round, while children above 18 months are asked these questions every 6 months.^29^ Starting in the second year of the trial, the six WHO motor milestones are measured on all children as appropriate for their age.^30^ Starting in the third year of the trial, all children have their weight recorded around 18 months of age. Every 4 months, women are asked about the different crop species grown in their gardens in the previous season (cool-dry, hot-dry, rainy) to assess diversity of production. Annually, questions are asked about dietary habits during Ramadan. Periodically, additional questions are added, for example, about poultry production, garden characteristics, household hygiene and food security.

Detailed quantitative food consumption information is recorded through dietary recall on a randomly selected subset of nine households per cluster, that is, a total of 864 households. To achieve even distribution over seasons and arms, the 96 clusters were divided into two phases of 48 clusters, with 24 intervention and 24 control clusters in each phase. Data are collected every 2 months, that is, six times per year, alternating between phases, with each cluster thus being visited three times per year to interview three households each time. Total food consumed by the household and how this was distributed among all household members is reported by the primary food preparer. A separate module about snacks and food intake between meals is asked to all available household members separately. In a third of the sample each round (one of the three households per cluster), diets are recorded on two non-consecutive days, less than 10 days apart, in order to enable estimation of usual intake and the proportion of the population at risk of inadequate intake. The methods used in data collection are derived from those designed by the International Food Policy Research Institute for the Bangladesh Integrated Household Survey.^31^ This procedure is repeated annually in the same households in the same season.

Birth registration activities are initiated on all identified pregnancies in the third trimester. Pregnant mothers are provided with free phone cards and encouraged to notify the team when they have delivered. An automated calling list is used by birth registration team members to give reminder calls to the pregnant women before their estimated date of birth. As soon as notified, ideally within 72 hours of birth, a trained female data collector visits the family, measures the newborn’s weight, length and head circumference, interviews the mother on the delivery, and provides initial breast feeding counselling. Birth registration data collectors are trained on standard anthropometric measurement techniques for newborns and calibrate measurement equipment on each day of use.

### Evaluation plan

#### Trial outcomes and measurements

##### Primary outcome

The primary outcome measure is length/height-for-age z-score in children under 3 years of age at endline, using the 2006 WHO child growth standards.^32^

##### Secondary outcomes

Secondary outcome measures include other measures of child growth, namely weight-for-length/height and head circumference-for-age z-scores in children 0–3 years; and length/height-for-age z-score in children 6–30 months, as well as growth outcomes at birth (length-for-gestational-age, weight-for-gestational-age and head circumference-for-gestational-age). For women’s nutritional status, indicators are BMI in non-pregnant women, and mid-upper arm circumference and gestational weight gain in pregnant women. Micronutrient status is measured through anaemia (haemoglobin), vitamin A deficiency (retinol-binding protein), iron deficiency (serum ferritin, soluble transferrin receptor) and zinc deficiency (serum zinc) in women and children, adjusting for inflammation (serum C-reactive protein, serum α−1-acid glycoprotein) when recommended (online supplementary table 2 and file 2).

Dietary diversity is measured according to published recommendations, using 10 food groups for women and 7 food groups for children.^26 29^ In addition, dietary adequacy is assessed for a subsample of women and children using the mean probability of adequate intake for 11 micronutrients (thiamine, riboflavin, niacin, vitamin B_6_, folate, vitamin B_12_, vitamin C, vitamin A, calcium, iron, zinc). Indicators for infections in children comprise 7-day period and 2-day point prevalences of diarrhoea and of acute respiratory infection. Early child development is assessed using WHO motor milestones.^30 33^

Food hygiene indicators include a hygiene behaviour score measured through structured observation in mothers with children 6–18 months of age, faecal contamination (total coliforms and *Escherichia coli*) of complementary food samples and enteropathy biomarkers (faecal myeloperoxidase, faecal α-1-antitrypsin, faecal neopterin, serum C-reactive protein, serum α−1-acid glycoprotein). This is conducted through the ‘Food Hygiene to reduce Environmental Enteric Dysfunction’ study nested into the FAARM trial (see online supplementary file 1).

##### Additional outcomes

The FAARM trial provides an ideal platform on which to explore other research topics, such as linkages between food production and diets, women’s agency and mental health, dietary influences on arsenic methylation capacity, mycotoxin exposure, (epi-)genetic factors influencing innate immunity and micronutrient metabolism, as well as diversity and composition of the mother’s and the child’s gut microbiome through which the above effects may be modified. Several of these additional research components will be explored during the course of the trial, contingent on time and funding.

##### Data collection

All measurements and samples are taken in accordance with current standards and methodology, building on questionnaire tools from HKI and James P Grant School of Public Health at BRAC University, including from the Food Security and Nutritional Surveillance Project in Bangladesh.^11^ HKI employs experienced field research assistants who receive specific training and supervision on anthropometric measurement and interview techniques. All blood sampling is undertaken by clinically trained staff, familiar with the appropriate methods of extraction, storage and processing.

Most trial outcomes are measured during the endline survey in late 2019 (figure 3). A week-long training is held for all data collectors, with separate trainings conducted for questionnaire interviewers, anthropometry and blood sampling staff, following standard measurement procedures.^34–36^ HKI staff conduct trainings for interviewers, covering survey question content, question-asking techniques and cultural sensitivity, and trainings for the anthropometry team, including standardisation exercises with local volunteers. Staff from icddr,b are responsible for training and supervision of blood and stool sampling and processing. Supervisors and trainers conduct quality control in the field and refresher trainings are given when needed. Data are collected via tablets and uploaded after each interview or at the end of the day. Datasets are examined for quality and adjustments to the questionnaires or refresher trainings with the data collectors are done as needed.

#### Data management

Questionnaires have been programmed to prevent common data collection errors. Data are compiled on a regular basis, and data quality checks are conducted. Data concerns are immediately communicated to the data collectors or research team for resolution. All quantitative and qualitative data are stored on password-protected servers and computers. Only deidentified data are shared with collaborators for analysis.

#### Statistical analysis plan

The main analysis will be to compare the mean length/height-for-age z-score in children, aged 0–35 months at the start of the endline survey, between intervention and control arms. This will be done using mixed-effects linear regression, that is, modelling between-cluster variation as a random effect in a full probability model. This method will be statistically more efficient than analysing results at the cluster level and also allows for analysis of individual-level covariates.^37^ In order to reduce between-cluster variation and thus increase power and precision of the study, we will adjust for baseline values of the main outcomes of interest (eg, mean length-for-age at cluster level) as well as potentially other relevant predictors. Secondary and other outcomes that are normally distributed will be analysed in the same way. Logarithmic transformation will be used for continuous variables with a skewed distribution (eg, agricultural yields). Binary outcomes (eg, health service use) will be analysed with mixed effects logistic regression models. Missing data on outcome measurements, including loss to follow-up, will be compared between intervention and control arms with respect to baseline covariates to assess the potential for selection bias.

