#### Sample size

The study sample size was calculated in relation to the primary outcome, length/height-for-age. A continuous z-score was used, that is, length/height in SD below or above the mean for a child of a given age and sex, which can then be translated into the percentage of children ‘moderately or severely stunted’ (below −2 SD). We aimed to detect a minimum difference of 0.20–0.25 in mean z-score at a 5% significance level. This effect size has been seen in studies using educational approaches to improve child growth.^16^

The sample size for each study arm was first calculated for a simple randomised design and then multiplied by a design factor to account for the clustered design as there is greater similarity of children’s nutritional status within a cluster. The intracluster correlation of length-for-age z-score was estimated to be 0.03, and for a minimum detectable effect size of 0.22 with 90% power, sample size was calculated as 677 children per arm, assuming a cluster size of 15. To account for loss to follow-up, possibly due to late refusal, withdrawal from the study or permanent migration out of the study area, an extra 10% was added. Therefore, we aimed for approximately 745 children per arm, 1490 children in total. Assuming an average of 15 children per cluster, born to 28 women, this meant that nearly 100 clusters needed to be randomised.

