#### Cluster randomisation

After the baseline survey, 96 clusters were randomly assigned to the intervention or control group (figure 3). We used covariate-constrained randomisation to ensure good balance, that is, that important baseline characteristics did not differ greatly between arms,^17^ using a self-programmed Stata routine.^18^ The randomisation was constrained by covariates on the cluster, household, woman and child level. (Cluster: union and number of women; Household: religion, food consumption score, household food insecurity access score, log of agricultural land size; Women: height, BMI, haemoglobin; Child: age, age-adjusted z-scores of length-for-age and weight-for-length, haemoglobin, diarrhoea prevalence.)

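### The reason given for covariate adjustment addresses the smaller part of the effect variance; the primary model should also commit to child age, child sex and mother's height

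*Protocol article*

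**What the plan says.** The Statistical analysis plan section of the Protocol article specifies a mixed-effects linear regression with cluster as a random effect. It notes that such a model can take covariates measured on individuals. The purpose given for adjustment is "In order to reduce between-cluster variation and thus increase power and precision of the study". The firm commitment is to baseline values of the main outcomes, with the cluster mean of length-for-age as the example. Further predictors are mentioned as possible but not named. The same section adds: "Secondary and other outcomes that are normally distributed will be analysed in the same way".

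The Sample size section supplies the variance inputs: "The intracluster correlation of length-for-age z-score was estimated to be 0.03", and "sample size was calculated as 677 children per arm, assuming a cluster size of 15", "for a minimum detectable effect size of 0.22 with 90% power".

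The Cluster randomisation section shows that maternal measurements were in hand before allocation and were used to constrain it: "Women: height, BMI, haemoglobin". By the Study design section, the children assessed at endline are conceived during the intervention, so they are not the children measured at baseline.

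**The concern.** In a cluster trial the variance of the treatment effect has two parts: true differences between clusters, and sampling of children within clusters. A cluster-level covariate can reduce only the first. If the second is larger, an adjustment strategy justified only by the first passes over the larger part. Individual-level covariates can reduce the second, and three are at hand: the child's age and sex, without which the z-score cannot be computed, and the mother's height.

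The named covariate is also imprecise. It averages a limited number of children who are not those measured at endline. What is at stake is precision and power for the primary comparison, which could be gained from data already collected.

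**Working it through.** **Inputs from the Sample size section.** Intracluster correlation ρ = 0.03; cluster size m = 15; difference 0.22; power 90%; 5% significance level, taken as two-sided because the article does not say; 677 children per arm.

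**Assumed, because the article gives no figure.** Fifteen baseline children per cluster; a correlation r between true baseline and endline cluster levels of 0.5, 0.8 or 1.0; a share R² of within-cluster variance explained by individual covariates of 5% to 20%.

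**The plan's own figure.** The design effect is 1 + (15 − 1) × 0.03 = 1.42. No SD is stated. An SD of 1.0 gives 435 × 1.42 = 618 per arm. An SD of about 1.048 gives 477 × 1.42 = 677, the stated figure. The loss allowance follows: 677 × 1.10 = 745. The ratios below do not depend on the SD.

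**Where the variance lies.** With total variance set to 1, the variance of a cluster mean is ρ + (1 − ρ)/m = 0.0300 + 0.97/15 = 0.0300 + 0.0647 = 0.0947. The variance of the effect estimate is proportional to this. The within-cluster share is 0.0647/0.0947 = 68.3%. At m = 15 this share is 77% for ρ = 0.02, 56% for ρ = 0.05 and 37.5% for ρ = 0.10, so the conclusion depends on the plan's low value.

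**What the baseline cluster mean can do.** Its reliability is λ = mρ/(1 + (m − 1)ρ) = 0.45/1.42 = 0.317 (0.24 with 10 baseline children, 0.38 with 20). The between-cluster part becomes ρ(1 − λr²). The effect variance therefore falls by 0.03 × 0.317 × r²/0.0947.

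**What individual covariates can do.** The within-cluster part becomes 0.0647 × (1 − R²), so the effect variance falls by 0.683 × R². Any between-cluster variance that they also explain is ignored.

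**Power.** Φ(3.2415/√VR − 1.96), where VR is the variance ratio after adjustment, 3.2415 = 1.960 + 1.2816, and the stated 90% is the unadjusted starting point.

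| Adjustment | Fall in effect variance | Power for 0.22 |
|---|---|---|
| None | 0% | 90% |
| Cluster mean, r = 0.5 | 2.5% | 90.7% |
| Cluster mean, r = 0.8 | 6.4% | 91.8% |
| Cluster mean, r = 1.0 (ceiling) | 10.0% | 92.7% |
| Individual, R² = 5% | 3.4% | 91.0% |
| Individual, R² = 10% | 6.8% | 91.9% |
| Individual, R² = 15% | 10.2% | 92.8% |
| Individual, R² = 20% | 13.7% | 93.7% |
| Both, r = 0.8, R² = 5% | 9.8% | 92.7% |
| Both, r = 0.8, R² = 20% | 20.1% | 95.2% |

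The last two rows match the precision of the unadjusted analysis with about 610 and 541 children per arm in place of 677. Individual covariates alone equal the cluster mean alone at R² = 3.7%, 9.4% and 14.7% for r = 0.5, 0.8 and 1.0.

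**The case against.** The strongest reply is that the article does not exclude individual covariates. It says the model can take them, gives the cluster mean only as an example, and leaves room for other predictors. The full list may stand in an analysis plan that is not shown, and a condensed article need not carry it. This is right, and a missing list is not the point. The point is that the stated purpose covers only the smaller variance component, and that the only firm commitment for the primary outcome follows that purpose.

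A second reply is that a cluster-level baseline is the natural choice, because endline children have no baseline z-score of their own. This also stands, and it is why the cluster mean should stay.

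A third reply is that the z-score is already standardised for age and sex, so what these still predict is unknown. The documents do not support calling the three covariates strong. Nor do they show that most of the attainable precision is being given up: at r = 0.8 the two kinds of adjustment contribute equally when R² is 9.4%.

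A reader might also infer that women's outcomes, analysed in the same way, will be adjusted only for a cluster mean. The text does not say so. The commitment is to baseline values, which naturally allows each woman's own value where one exists; the cluster-level example belongs to length-for-age.

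**Conclusion.** The point holds as a low-cost improvement in efficiency. At the plan's own intracluster correlation and cluster size, about 68% of the variance of the effect estimate is within clusters. This share refers to the effect estimate; of the variance of a single child's z-score, 97% is within clusters. The covariate named for the primary outcome cannot reduce that part and can remove at most about 10% of the effect variance. Adding individual covariates would bring power for 0.22 from 90% to about 91% to 94% alone, or to about 93% to 95% together with the cluster mean at r = 0.8.

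These gains rest on the assumed R² and r, on 15 baseline children per cluster, on equal cluster sizes and on a normal approximation. They also assume that the intervention does not shift the age or sex of the children assessed, who are conceived after allocation.

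A reader might infer that the planned analysis is biased or the trial underpowered. Neither follows. The stated sample size reaches 90% power without counting on any adjustment, and the model as described is valid.

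**What to change.** Keep the baseline cluster mean of length-for-age. Before unblinded analysis, commit to three fixed individual-level covariates in the primary model: child age at measurement in a flexible form (spline or age bands), child sex, and the mother's own baseline height. Widen the stated purpose of adjustment to cover variation both between and within clusters. Mother's height has a further claim, since it constrained the randomisation.

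Women who joined by marriage during the first year of implementation may have no baseline height, so state a simple rule for missing covariates, such as mean imputation with a missingness indicator.

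The cost is a few sentences of analysis wording. No new data are needed, and the design and sample size are unchanged.

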### Patients and public involvement

Participants were not involved in the study design or in the setting of research objectives or outcomes. Intervention implementation is adapted to participant concerns and constraints. Key stakeholders will be involved in dissemination of research findings.

### Dissemination

#### Consent

All enrolled FAARM participants provide informed, written consent by signature or thumbprint if illiterate, for themselves and for their children, if applicable. All participants receive an information sheet with contact information of the local FAARM manager for any questions or concerns.

#### Risks and benefits

The risks from participation (time expenditure over 4 years, anthropometric measurement and biological sampling) are minimal when compared with the potential knowledge gained from this study. There are some benefits for all participants, including referral for serious conditions when detected during surveys, early pregnancy identification (through distribution of pregnancy tests) and initial breast feeding counselling. Participants in the intervention arm additionally benefit from intervention activities in the form of assets, training and support to adopt promoted behaviours.

All participants are informed about their anthropometric measurements in cases of low BMI or child growth, and haemoglobin values when anaemic. The results of the trial will be disseminated to all research and implementation partners, published in peer-reviewed journals, and presented at national and international conferences and events. Programme and policy-related findings will be distributed through the HKI network and other agricultural and nutrition fora.

#### Project status

As of April 2019, participant enrolment, baseline survey and intervention activities have been completed. The surveillance activities are ongoing and the endline survey is planned for late 2019.

## Discussion

To our knowledge, this is the first randomised controlled trial to assess the impact of a complex, nutrition-sensitive agricultural programme on children’s nutritional status that enrols women prior to pregnancy, thus capturing the first 1000 days of child development. It is particularly relevant and well placed in rural Bangladesh where stunting and micronutrient deficiencies are common. We will be able to assess whether the intervention has impacted each outcome and how this occurs, due to a comprehensive monitoring and surveillance system through which we track programme fidelity and intensity, participation and outcomes along impact pathways. By assessing participant knowledge and behaviours as well as anthropometric and biological measures, we will be able to examine changes on a wide range of indicators. In addition, the rotating data collection pattern of the surveillance system will allow the project to map out changes in diets over seasons and between intervention and control households over time. Data on the sources of foods consumed by households will enable tracking of changes in food consumption habits, comparing garden production to market purchases. A limitation of our study is the lack of continuous child growth monitoring and blood sampling during surveillance, due to financial and logistic constraints. Data collection of children will also end at 3 years of age, which may miss growth or child development impacts which appear later.

We expect that the findings from this trial will contribute to national policy discussions regarding the contribution of complex nutrition-sensitive agricultural interventions to improving nutritional status and other outcomes. Furthermore, trial results may be generalisable to other settings where poverty, food insecurity and climate change affect nutrition and health.

10.1136/bmjopen-2019-031037.supp3Supplementary data

10.1136/bmjopen-2019-031037.supp4Supplementary data
